### Sample size calculation

The failure rate of NCPAP with MISA approach was 24.5% (of NIPPV, 22.4%) in preterm infants aged <32 weeks with RDS (15). There was no statistical difference between the two groups. We have set the non-inferiority margin for the trial at 10%. That is, NCPAP is supposed to be non-inferior to NIPPV if the difference in risk of NCPAP treatment failure and the upper limit of its bilateral 95%CI is <10%. To demonstrate this with 80% power, 452 infants per study group are required. In order to prevent the loss of samples, the sample size is increased by 6%. Therefore, a total of 960 samples will be selected and allocated randomly 1:1 into the two study groups (480 in the NCPAP group and 480 in the NIPPV group).

### Statistical analysis

#### Baseline data

Demographic and clinical characteristics for the NCPAP group and the NIPPV group at baseline will be described in mean and standard deviation, median and range, or rate and percentage. Continuous variables will be presented in mean ± standard deviation or median (minimum-maximum), and categorical variables will be presented in numbers and proportions. We will not test the hypothesis with the two sets of baseline data.

#### Outcome data

The data will be analyzed based on the original treatment allocation of the participants in accordance with the intention-to-treat principle. To compare the primary and secondary outcomes between the two groups, we will use the Student's *t*-test for continuous variables (if normally distributed), the Mann-Whitney U test (if skewed) and the *chi*-squared test for categorical variables. In addition to the *p*-value of the outcomes, results are to be given in terms of differences and 95% CIs. Preplanned exploratory subgroup analyses are to be performed for the primary and other pre-specified outcomes by gestational age, and birth weight. All data will be analyzed using SPSS version 20.0. Two-tailed *p-*values <0.05 will be considered as statistically significant.

## Discussion

In recent years, most studies have shown that NIV reduces the risk of BPD in preterm infants when compared to intubation and IMV (5, 22). Previous trials have reported that MISA during NIV further minimized the need for IMV and the incidence of BPD in very low birth weight infants with RDS (23, 24). NIV modes commonly used in NICUs include NCPAP, NIPPV, bi-level positive pressure and high flow nasal cannula, of which NCPAP and NIPPV are the two most common modes (7, 25). The goal of NCPAP is to maintain the functional residual capacity for reducing breathing effort. Early use of NCPAP is an alternative to intermittent positive-pressure ventilation and intubation (26). However, NCPAP has a high failure rate and requires IMV in the first 72 h−7 days of life, especially in extremely low birth weight infants. This is due to the immature respiratory center, poor diaphragmatic strength and chest wall collapse in these infants (27). NIPPV superimposes an intermittent peak pressure on NCPAP. Some studies have shown that NIPPV is superior to NCPAP after extubation (8, 28, 29). A Cochrane meta-analysis of 10 studies involving 1,431 infants compared the effects of NIPPV and NCPAP on respiratory support after extubation and reported that NIPPV reduced the incidence of respiratory respiratory support failure [RR: 0.70 (95% CI 0.60, 0.80)] and reintubation [RR: 0.76 (95% CI 0.65, 0.88)] more effectively than NCPAP (8). Ferguson et al. suggested that NIPPV was more effective than NCPAP in preventing extubation failure (30).

At present, it is still controversial whether NIPPV is superior to NCPAP in initial non-invasive respiratory support for premature infants, especially for those with a gestational age of <30 weeks. A meta-analysis of 1,061 infants recruited in 10 trials shows that early NIPPV seems to reduce the need for intubation and IMV in premature infants with RDS than NCPAP alone (9). A small clinical study shows that initial NIPPV enhances the beneficial effects of NCPAP as non-invasive respiratory support, contributing to reducing the risk of treatment failure in very low birth weight infants with RDS (31). However, one large randomized controlled trial involving 1,009 patients with a birth weight of <1,000 g, comparing NIPPV with NCPAP, shows no difference in non-invasive support failure (58.3 vs. 59.1%) and survival with BPD (33.9 vs. 31.0%) (32). In a multicenter retrospective cohort study involving 512 preterm infants with RDS, NIPPV was not found to be more effective than NCPAP in decreasing the need for IMV within the first 7 days of birth (33). A randomized controlled trial shows that among infants born between 26 and 32 weeks of gestation, NIPPV as the initial respiratory support with MIST reduced the need for IMV (13 vs. 29%; *p* = 0.005) and the rate of moderate-to-severe BPD (7 vs. 16%; *p* = 0.046) compared with NCPAP, however, this was not seen for the subgroup of preterm infants of a gestational age of <30 weeks (20 vs. 32%; *p* = 0.16) (16). Therefore, carefully designed and larger randomized controlled trials are needed for infants of a gestational age of <30 weeks.

In this multicenter randomized controlled trial, we put forward the hypothesis that NCPAP is not inferior to NIPPV as the initial respiratory support before MISA in reducing the use of IMV in preterm infants aged <30 weeks. The study will provide some data for the selection of initial NIV mode in preterm infants with a gestation age of <30 weeks with spontaneous breaths. Nevertheless, there are some potential limitations in our study design: (1) Preterm infants with spontaneous breaths will not be grouped immediately after birth, but upon arrival in NICUs. We stipulate that non-invasive respiratory should be supported with transport ventilator or T-piece during delivery room resuscitation and transfer, and we will limit the time to arrive at the NICUs to within 30 min after birth. (2) Treatment allocations (in a 1:1 ratio) will be based on a pre-specified random number table, without stratification according to gestational age and birth weight. This is due to the fact that the estimated sample size of premature infants at 24–26 weeks with spontaneous breaths after birth and without intubation during delivery room resuscitation is relatively small. (3) The diagnosis of RDS will be made based on clinical manifestations and Silverman Anderson Score, without classification of RDS severity.

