## Methods

### Study design

The NIV-MISA-RDS trial is a multicenter, randomized, non-inferiority trial, conducted in preterm infants <30 weeks' gestational age requiring primary non-invasive respiratory support for respiratory distress in the first 2 h of life. The trial will be conducted in 14 centers and carried out according to the prospective trial flow shown in Figure 1. All hospitals where the participating NICUs are located are midwifery institutions with an annual delivery of more than 3,000 newborns. All the participating NICUs are level three facilities with a more than 50% survival rate of premature infants 24–30 weeks in the past 3 years before the initiation of the study. Before delivery, a multidisciplinary consultation will be made, and a neonatologist will communicate with the family, as premature deliveries at 24–30 weeks involves many risks. A neonatal resuscitation team will be set up before the deliveries for the implementation of neonatal resuscitation with T-piece, non-invasive ventilation for preterm infants with spontaneous breaths. The neonatal resuscitation teams will use the transfer warmer for in-hospital transfer, and will use the T-piece device during transfer until admission of infants into NICUs. All infants will start either NCPAP or NIPPV by ventilators in NICUs after randomization. Pulmonary surfactant will be made available, and once diagnosis of RDS is made, PS will be administered within 120 min after birth. All neonatologists in the 14 centers have routinely taken care of preterm infants with respiratory distress and have used NIV as their standard mode of primary respiratory support. They have been trained for neonatal resuscitation and MISA. Individual practice and team training are required to sustain knowledge and skills.

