### Randomization

After transfer to NICU wards, eligible infants will be randomly assigned in a 1:1 ratio to receive either NCPAP (experimental group) or NIPPV (active control group) as the initial respiratory support. Treatment allocations will be based on a pre-specified random number table and concealed in sealed opaque envelopes. The treatment allocations sequence will be generated using computer programs (R software) by an independent statistician. Multiple-birth infants will be randomized separately.

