#### Data collection and diagnoses

Patient demographic data mainly include: gestational age, birth weight, sex, multiple births, antenatal corticosteroids use, mode of delivery, maternal complications, Apgar score and cord blood gas. Clinical data mainly include: SAS, requiring more than one dose of surfactant, blood gas, the need for IMV within 72 h and 7 days after birth, duration of NCPAP/NIPPV, days on IMV, days on supplemental oxygen, costs associated with hospital care, morbidity of BPD, pneumothorax, nasal trauma, pulmonary hemorrhage, hsPDA, IVH, white matter injury, blood culture-confirmed sepsis, NEC and ROP.

The clinical diagnosis of RDS will be based on clinical manifestations (respiratory rate > 60/min, nasal flaring, retractions, grunting, or skin cyanosis) and (FiO_2_) > 0.3 for (SpO_2_) > 85%, or SAS > 5 points or SAS increasing > 2 points per hour (17). BPD will be diagnosed according to the National Institutes of Health criteria (18). Pneumothorax will be diagnosed by the presence of air in the pleural cavity in a chest X-ray. Pulmonary hemorrhage will be diagnosed based on the gushing of bloody fluid from the upper airway or endotracheal intubation and when the chest X-ray is consistent with the relevant clinical findings. The diagnosis for hsPDA will be based on clinical signs and echocardiogram (19). IVH and white matter injury will be diagnosed by cranial ultrasound examination, and IVH will be graded by the Papile classification system (20). Blood culture-confirmed sepsis will be defined as clinical sepsis with evidence of pathogens in blood culture. NEC will be graded according to the modified Bell's classification system (21). The diagnosis and staging of ROP will be based on retinal examination by a consultant ophthalmologist.

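### The primary risk difference is planned without adjustment for gestational age, which gives up some precision that baseline data already collected could recover

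*Protocol article*

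**What the plan says.** All places are in the protocol article.

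- **Randomization:** "Treatment allocations will be based on a pre-specified random number table and concealed in sealed opaque envelopes". The ratio is 1:1 and no stratification factor is named.
- **Discussion (limitations):** allocation is "without stratification according to gestational age and birth weight". The reason given concerns expected numbers: "the estimated sample size of premature infants at 24–26 weeks with spontaneous breaths after birth and without intubation during delivery room resuscitation is relatively small".
- **Outcome data:** the method is fixed in one sentence, opening "To compare the primary and secondary outcomes between the two groups, we will use" and naming, for non-normal and categorical outcomes, "the Mann-Whitney U test (if skewed) and the *chi*-squared test for categorical variables". Differences and 95% CIs accompany the p-values. Gestational age and birth weight appear only in exploratory subgroup analyses. Centre does not appear. SPSS 20.0 is named for all analysis.
- **Data collection and diagnoses:** the baseline items recorded include "gestational age, birth weight, sex, multiple births, antenatal corticosteroids use".
- **Sample size calculation:** failure 24.5% (NCPAP) and 22.4% (NIPPV), margin 10 points, two-sided 95% CI, 80% power, 452 per group, raised to 480.
- **Discussion:** the high NCPAP failure rate is said to be most marked in extremely low birth weight infants, and is attributed to their immaturity.

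**The concern.** The document identifies immaturity as a driver of the primary outcome, records gestational age at baseline and concedes that allocation does not balance it, but the primary analysis makes no use of it. The outcome variance that gestational age explains therefore stays in the standard error of the risk difference.

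Scarcity of infants at 24–26 weeks can be a reason not to form strata at randomisation. It is no reason against covariate adjustment, which needs no strata.

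Centre is a plausible second factor. "The trial will be conducted in 14 centers", clinicians are unblinded, failure includes the need for intubation, and one intubation criterion under Therapy is the neonatologist's own judgement. The document does not say that thresholds differ between centres; that is a supposition.

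At stake is the width of the CI that is set against the margin. Timing matters as well: an adjustment chosen after an imbalance has been seen, with a result close to 10 points, would look data-driven.

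**Working it through.** **1. The plan's own figure.** Inputs from Sample size calculation: 0.245, 0.224, margin 0.10, one-sided 2.5%, power 80%.

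- Distance to the margin: 0.10 − (0.245 − 0.224) = 0.079.
- Variance sum: 0.245 × 0.755 + 0.224 × 0.776 = 0.3588.
- n = (1.960 + 0.842)² × 0.3588 / 0.079² ≈ 451.2, so **452 per group**, an exact match for an unadjusted comparison.
- At 452 per group: SE = √(0.3588/452) = 2.82 points, CI half-width 5.52 points, power = Φ(7.9/2.82 − 1.96) = 80.1%.
- At 480 per group: SE = 2.73 points, power 82.4%.

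**2. Effect of adjustment.** If baseline factors explain a share R² of outcome variance, the variance of the difference is multiplied by about (1 − R²). R² is not in the document, so a range is shown.

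| R² (assumed) | Power at 452 | CI half-width (points) | n per group for 80% |
|---|---|---|---|
| 0 | 80.1% | 5.52 | 452 |
| 2% | 80.9% | 5.47 | 443 |
| 5% | 82.0% | 5.38 | 429 |
| 10% | 84.0% | 5.24 | 407 |
| 15% | 86.0% | 5.09 | 384 |
| 20% | 88.0% | 4.94 | 362 |

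**3. Which R² is plausible?** Assumptions: shares of 2, 5, 10, 18, 28 and 37% for weeks 24 to 29; an odds ratio for failure of 1.2 to 2.0 per week of lower gestation; a centre SD of 0 to 0.6 on the logit scale; overall failure about 23.5%. These give R² from 1.1% (power 80.5%) to 18.8% (power 87.5%).

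A rough cross-check uses the trial below 1,000 g cited in the Discussion, where support failed in about 59%. It is a different study with its own definition, so this only illustrates. Suppose 10% to 20% of infants failed at 59% within an overall 23.5%.

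- At 10%: the others fail at (0.235 − 0.059)/0.9 = 19.6%, and R² = 0.1 × 0.9 × 0.394² / 0.180 ≈ 8%.
- At 20%: the others fail at (0.235 − 0.118)/0.8 = 14.6%, and R² = 0.2 × 0.8 × 0.444² / 0.180 ≈ 17%.

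Power would be about 83% to 87%.

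**4. Simulation.** 4,000 trials per scenario, 452 per group, simple randomisation, 14 centres with SD 0.3. The unadjusted difference is compared with a standardised logistic estimate adjusted for week and centre.

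| Odds ratio per week | Power, unadjusted | Power, adjusted | Error at margin, unadjusted | Error at margin, adjusted |
|---|---|---|---|---|
| 1.4 | 80.1% | 82.0% | 2.9% | 3.2% |
| 1.6 | 79.2% | 83.0% | 2.4% | 2.5% |
| 2.0 | 79.6% | 86.0% | 2.9% | 3.2% |

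The unadjusted estimate averaged 2.09 to 2.17 points for a true 2.1, so it is unbiased. The Monte Carlo SE of an error rate near 2.5% is √(0.025 × 0.975/4000) ≈ 0.25 points. The unadjusted rates are therefore near nominal; two of the adjusted rates lie slightly above it. The gain is not just a looser test: the SD of the estimate fell from 2.78 to 2.73, from 2.84 to 2.73 and from 2.81 to 2.60 points, which is a variance reduction of about 4%, 7% and 14%.

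**5. Size of chance imbalance.** At 480 per group and under the assumptions in step 3, imbalance moves the difference with an SD of √(2 × R² × 0.2345 × 0.7655/480), or 0.3 to 1.2 points. This is a component of the 2.73-point SE, not an addition to it.

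**The case against.** The strongest reply is that nothing is broken. The unadjusted CI already allows for chance imbalance, the error rate at the margin is near nominal, and the sample size is correct for the analysis stated. If all 480 per group are evaluable, unadjusted power is already 82.4%, about what adjustment would give at 452 with R² of 5% to 6%. The gain rests wholly on assumed prognostic strength, the missing stratification is disclosed as a limitation, and an adjusted sensitivity analysis may be in a SAP that is not shown. All of this stands, and it limits the point to efficiency. It does not remove it: the article states the primary method rather than leaving it open, and a gain from adjustment would come on top of the 82.4%.

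A reader might infer more than the document supports:

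- **That a prognostic imbalance is known to exist, or biases the result.** None is documented. As an extreme case, take an assumed 100 infants at 24–26 weeks split 40:60. That is 20/480 = 4.2 points of arm composition; with an assumed 30-point gap in risk it shifts the difference by 1.25 points, against a half-width of 1.96 × 2.73 = 5.4 points.
- **That randomisation ignores centre.** The article names only gestational age and birth weight as not stratified. It is silent on whether lists or envelopes were prepared by centre, and an article commonly leaves that to the full protocol.
- **That the list ought to be stratified.** Sparse strata are a recognised reason not to: 14 centres by two gestational bands is 28 strata, with about 100/14 ≈ 7 of those assumed 100 infants per centre. That is a trade-off, not an error.

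**Conclusion.** The point holds as one of efficiency, not validity. The planned unadjusted comparison is unbiased and meets its stated 80% power at 452 per group. It leaves removable variance in the result although gestational age is recorded and the document links failure to immaturity. The gain from adjustment is about 0.5 to 7.5 percentage points of power at 452 per group. That range depends on the assumed gestational-age distribution, weekly odds ratio and centre variation, none of which the document gives. The case for gestational age rests on the document's own account of immaturity; the case for centre is plausible only.

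**What to change.** Pre-specify, before outcome data are seen, that the primary estimate is the risk difference adjusted for gestational age in weeks as a continuous covariate, and for centre as a further factor. Logistic regression with marginal standardisation keeps the target as the same overall risk difference. Report a robust 95% CI and compare its upper limit with the 10-point margin. Allow for the number of covariates in the variance estimate, and check the error rate at the margin by simulation, since two of the three adjusted scenarios came out slightly above 2.5%. Keep the unadjusted difference and CI as a supportive analysis. The randomisation list need not change.

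The cost is some added wording and programming, with no extra infants or data. The analysis becomes slightly more complex and would probably need software other than SPSS 20.0, so the software statement in Outcome data should be amended. R is named only for generating the allocation sequence.

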## Conclusion

If, as expected, NCPAP is non-inferior to NIPPV, it will provide an opportunity to increase the availability of NCPAP treatment for preterm infants of a gestational age of <30 weeks with spontaneous breaths.

## Ethics statement

The studies involving human participants were reviewed and approved by Peking University Third Hospital Medical Science Research Ethics Committee (Project Number: M2021378). Written informed consent to participate in this study was provided by the participants' legal guardian/next of kin.
